**Methods/design:**

An open-label multi-center randomized controlled trial is being conducted at different CR centers from three Swedish University Hospitals. The aim is to include 150 patients with MI < 75 years of age who are confident smartphone and/or Internet users. In addition to participation in CR programs according to the usual routine at each center, patients randomized to the intervention arm will receive access to the web-based app. A CR nurse reviews the patients’ self-reported data twice weekly through a medical interface at the clinic. The primary outcome of the study will be change in submaximal exercise capacity (in watts) between 2 and 4 weeks after discharge and when the patient has completed his/her exercise program at the CR center, usually around 3–6 months post-discharge. Secondary outcomes include changes in self-reported physical activity, objectively assessed physical activity by accelerometry, self-rated health, dietary, and smoking habits, body mass index, blood pressure, blood lipids, and glucose/HbA1c levels between inclusion and follow-up visits during the first year post-MI. Additionally, we will assess uptake and adherence to the application, the number of CR staff contacts, and the incidence of cardiovascular events at 1 and 3 years after the MI. Patient recruitment started in 2016, and the first study results are expected in the beginning of 2019.

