### Usual care

All patients, in both the control arm and the intervention arm, will be offered participation in CR programs according to the usual routine at each center. The CR programs at the three study centers have approximately the same follow-up protocol, as they all report to the SEPHIA registry, which requires data registration at fixed time points. Minimally, the CR program includes five out-patient visits at the CR center. The patient’s first contact is with a CR nurse within 2–4 weeks from discharge (*t*1), closely followed by a first physiotherapist visit (*t*2) at which a symptom-limited bicycle ergometer test is performed (Fig. 2). A second nurse or physician visit (*t*3) is offered at 6–10 weeks post-discharge. A follow-up visit with a physiotherapist (*t*4) is offered when the patient has completed his/her exercise program at the CR center, usually around 3–6 months post-discharge. A second ergometer test is performed at the *t*4 visit. At 6–8 months, laboratory measures of lipids and glucose/HbA1c are performed (*t*5), followed by a telephone call in case of abnormal results. A last visit to a nurse (*t*6) is offered at 12–14 months after the index event. Information on lifestyle (exercise, daily physical activity, diet, and smoking), risk factor levels (blood pressure, weight, waist circumference, fasting plasma glucose, Hb A1c, serum lipids), and self-rated health (measured with the EQ-5D quality of life (QoL) questionnaire and a general self-rated health visual analog scale 0–100) are controlled at the nurse and physiotherapist visits according to Fig. 2 [19].

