#### The medical interface

All information that the patients log in the app is transferred to a medical interface that can be accessed by the treating nurses, physiotherapists, and physicians at the CR center. Additionally, the system ranks the patients, giving high priority for example to patients reporting chest pains, not taking their medications, or who are lagging behind with their exercise regime, while patients that follow recommendations and are doing well receive a lower ranking (Fig. 4). This information is reviewed by the CR nurse twice weekly. The algorithm in the LifePod® system thus gives priority support for the healthcare professional based on the patients’ reported outcomes. This allows for targeted interventions and better resource management. In addition, the system gives the caregiver the opportunity to manage and guide both individual patients (1:1 follow-up) and large patient populations (1:1000 or more).

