#### Secondary outcomes

The secondary outcomes are described as follows:Changes in the following variables measured from inclusion to first, second, and third nurse visits, respectively:Self-reported health using the visual analog scale (see Additional file 1)Healthy diet index as evaluated within SEPHIA (see Additional file 1)Smoking habits (self-reported)Weight (kilograms), body mass index (BMI, in kilograms/meter^2^), and waist circumference (in centimeters)Systolic and diastolic blood pressure (mmHg)Total cholesterol, low-density lipoprotein and high-density lipoprotein cholesterol, and triglycerides in plasmaFasting plasma glucose and HbA1cChanges in self-reported physical activity (by Haskell and Frändin and Grimby; see Additional file 1) measured from inclusion to first and second physiotherapist visits, respectively [23, 24]Uptake (proportion of patients who log on to the patient interface at least once) and adherence (proportion of patients registering data at least twice per week on a weekly basis throughout the intervention period)Number of telephone and physical contacts with the CR staffIncidence of cardiovascular events at 1 and 3 years after the index event: hospitalization for a new MI, heart failure or stroke, and cardiovascular deathCorrelations between self-reported physical activity levels and objective measurements of physical activity and sedentary time measured by a validated instrument for 7 consecutive days, as analyzed using ActiGraph accelerometers. ActiGraph accelerometers are widely used in research because they have shown high validity and reliability [25, 26]. The measurements will be performed in conjunction with the first and second physiotherapist visits (*t*2 and *t*4) on patients recruited at Skåne University Hospital in Malmö (*n* = 60).

As recruitment was finalized in April 2018 and patients are followed for 1 year, the final study results will first be available by the fall of 2019.

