### Statistical analysis, power, and sample size

Sample size calculations were based on results from a local registry (SEPHIA) data analysis including 40 post-MI patients attending CR at one of the study centers (Skåne University Hospital in Malmö). Out of the 40 patients included in the analysis, 73% participated in a hospital-based exercise program, on average 7 times (range 2–12) during an 8-week exercise period. The difference (Δ) in cardiac exercise capacity (W), measured using a symptom-limited bicycle ergometer test at 2–4 weeks post-discharge and after completing a hospital-based exercise program (around 3–6 months post-discharge), was calculated. The average difference was + 14.6 (± 15.6) W. With a power of 90%, a two-sided significance level of 0.05, and a least mean difference at 10 W (standard deviation (SD) ± 20 W) between groups, the estimated sample size was 150 patients: 50 patients in the usual care arm and 100 patients in the intervention arm. This included an intention-to-treat dilution effect based on a 40% loss of adherence in the intervention arm, an estimation based on our own feasibility study as well as other studies reporting adherence to eHealth interventions in CR [11, 13–15, 17]. The study is not powered to detect effects on major adverse cardiac events. As such, these analyses will only be exploratory.

Differences in outcomes between the control arm and intervention arm will be performed using an independent samples *t* test (continuous variables) and a chi-square test (categorical variables). If differences in baseline characteristics, number of follow-up visits, or telephone contacts are observed, linear and logistic regression analysis will be applied, adjusting for the observed differences between the two study arms.

A full study protocol and a Standard Protocol Items: Recommendations for Interventional Trials (SPIRIT) checklist (recommended items to address in a clinical trial protocol and related documents) are provided as additional files (Additional files 1 and 2).

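### The adjustment rule covers visits and telephone contacts, which arise after randomisation and overlap a listed outcome; if the app changes them and they relate to the outcome, the adjusted estimate is biased for the total effect

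*Protocol article*

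**What the plan says.** Under *Statistical analysis, power, and sample size*, the protocol article first specifies an unadjusted comparison: "Differences in outcomes between the control arm and intervention arm will be performed using an independent samples" *t* test for continuous variables, with a chi-square test for categorical ones. It then adds a conditional rule: "If differences in baseline characteristics, number of follow-up visits, or telephone contacts are observed, linear and logistic regression analysis will be applied". The regression is meant to correct for whatever imbalance between the arms is found. One rule therefore covers three kinds of variable: baseline characteristics, number of visits, and number of telephone calls. It gives no threshold for an observed difference and does not rank the two analyses.

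Four other places bear on this:

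- *Secondary outcomes* lists the number of "telephone and physical contacts with the CR" staff, and the abstract repeats it: "we will assess uptake and adherence to the application, the number of CR staff contacts".
- *The medical interface* describes a priority ranking of intervention patients built from what they log. "This information is reviewed by the CR nurse twice weekly". The stated benefit is: "This allows for targeted interventions and better resource management".
- *Usual care* says that the laboratory measurement at t5 is "followed by a telephone call in case of abnormal results".
- *Aim of the study* compares the web application, added to CR, with usual care.

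**The concern.** A covariate in a randomised comparison should not be something the treatment can change. Visits and calls accumulate during follow-up, and only one arm has the app and the nurse review attached to it. A between-arm difference in contacts may therefore be part of what the app does.

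Adjusting for contacts can go wrong in two ways. If contacts carry part of the benefit, adjustment removes that part. If contacts and outcome share causes, for example because patients who are doing badly are called more often, adjustment links arm to outcome through those causes and can produce a difference where none exists. For lipids and glucose/HbA1c the problem is more direct, because some calls follow from abnormal values of those same secondary outcomes.

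What is at stake is whether the reported estimate answers the question in the aim. The article sizes the trial with an intention-to-treat dilution, so the total effect of being assigned the app is what it sets out to measure.

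**Working it through.** **The passages side by side.** Visits and telephone calls appear as adjustment variables in the analysis section. Telephone and physical contacts appear as an outcome under *Secondary outcomes* and in the abstract. The two lists overlap. *The medical interface* gives a route from app to contacts, and *Usual care* gives a route from measured outcomes to calls. Nothing in the article calls the adjusted model a mediation or sensitivity analysis.

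**What adjustment does.** Measure contacts in SD units. Let *a* be the between-arm difference in contacts and *s* the within-arm slope of watt change on contacts (W per SD), whatever its cause. In a linear model:

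expected adjusted estimate = total effect − *a* × *s*

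The bias is zero only if *a* = 0 or *s* = 0. Its sign depends on the signs of both. The article gives neither quantity.

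**Inputs from the article.** 50 control and 100 intervention patients, SD 20 W, difference 10 W, two-sided 0.05.

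**Reference point.** The standard error is 20 × √(1/50 + 1/100) = 3.46 W, so the unadjusted test has power Φ(10/3.46 − 1.96) = Φ(0.93), about 82%. The article states 90% for this sample size. That mismatch is a separate matter and nothing below depends on it.

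**Assumed inputs (not in the article).** The values of *a* and *s*, and, for the rule as written, a trigger of p < 0.05 for the difference in contacts. In the fourth and fifth rows, a prognostic factor lowers watt change by 8 W per SD and correlates 0.5 with contacts, so *s* = −8 × 0.5 = −4. In the sixth and seventh rows, contacts correlate −0.25 with watt change, so *s* = −0.25 × 20 = −5. Simulated means over 4000 trials per scenario agree with the formula.

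| Scenario | *a* | *s* | Total − *a*×*s* (always adjusted) | Rule as written | Rejection rate: t test → always adjusted |
|---|---|---|---|---|---|
| True 10 W, half through contacts | 0.8 | 6.25 | 10 − 5.0 = 5.0 W | 5.0 W | 83% → 30% |
| True 10 W, a quarter through contacts | 0.5 | 5 | 10 − 2.5 = 7.5 W | 7.8 W | 82% → 58% (60% under the rule) |
| True 10 W, app does not change contacts | 0 | 5 | 10.0 W | 10.0 W | 82% → 85% (82% under the rule) |
| True null, contacts rise | 0.5 | −4 | +2.0 W | +1.8 W | 4% → 8% |
| True null, contacts rise more | 0.8 | −4 | +3.2 W | +3.2 W | 4% → 14% |
| True null, contacts rise | 0.5 | −5 | +2.5 W | +2.3 W | nominal 5% → 11% (10% under the rule) |
| True null, contacts fall | −0.5 | −5 | −2.5 W | same size as the row above, sign reversed | nominal 5% → 11%, by symmetry |

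**The condition does not protect.** With a 0.5 SD difference in contacts the assumed trigger fired in about 82% of simulated trials, and with 0.8 SD in over 99%. With no difference it fired in about 4%. So the rule mostly adjusts when the app has changed contacts, and then gives nearly the same answer as always adjusting.

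**The case against.** The strongest reply has four parts.

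- **The rule is conditional and follows an unadjusted test.** A reader might infer that the plan always adjusts and that its result is therefore biased. The text does not support that. Adjustment happens only if differences are seen, and if the app leaves contacts alone there is no bias. What remains is that the condition selects the harmful case.
- **Replacement is not stated.** A reader might infer that the regression displaces the t test. The article does not say so, nor does it say that the t test stays primary, and the full protocol to which it refers is not at hand. If the adjusted model is only supportive, the damage is to interpretation and not to the main result. That limits the consequence but does not make the rule sound.
- **The app is not said to generate contacts.** A reader might infer that nurse review triggers calls or visits. *The medical interface* says only that it allows targeted interventions and better resource use, which fits fewer contacts as well as more. The visit schedule offered is also common to both arms. A changed number of contacts is plausible, but its direction is unknown.
- **The figures rest on assumptions.** The mediation rows simply subtract the share assumed to run through contacts. No row is an estimate for this trial.

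The last two points stand in full as limits on the claim. None of the four justifies adjusting a total effect for contacts.

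**Conclusion.** The point holds in conditional form. The rule as written tells the analyst to adjust for post-randomisation variables that overlap a listed outcome. If the app changes visits or contacts, and these are related to the outcome, the adjusted estimate is biased for the effect of app plus CR versus usual CR. The bias can go either way and its size cannot be obtained from the article. Under the assumptions shown it ranges from none to half of a 10 W effect, or 2.0 to 3.2 W in either direction under a true null for contact differences of 0.5 to 0.8 SD.

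The seriousness depends on which analysis is the headline, and the article leaves that open. The baseline part of the rule does not share this fault, although choosing covariates by observed imbalance is data-driven.

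**What to change.** Amend the analysis section as follows:

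1. Remove follow-up visits and telephone contacts from the adjustment rule, both as trigger and as covariates.
2. State that the comparison unadjusted for visits and contacts is the main result.
3. Restrict covariates to variables fixed before randomisation. The first ergometer test (t2) needs care. Patients are recruited within 2 weeks of the infarction, preferably in the coronary care unit, and intervention patients may meet the software during admission, whereas t2 falls 2–4 weeks after discharge. If the t2 value is used as a covariate, say that it appears to be measured after randomisation and could be affected by the app.
4. Report visits and contacts by arm as outcomes.
5. Label any analysis of whether contacts explain the effect as an exploratory mediation analysis.

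The cost is a few sentences and no new data. Recruitment is complete, but the article places the final results later, so the wording could be changed before the final analysis.

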## Discussion

Using the Internet and smartphones opens an array of new opportunities on how to provide care. It allows us to move away from a calendar-driven type of healthcare, where communication between patients and healthcare professionals is limited to booked appointments at a healthcare facility, to an individual-tailored type of care, where the patient can access information, receive advice independently of place and time, and take control over his or her treatment in a whole new way. Accordingly, the interest in eHealth solutions has grown exponentially during the last years, equally so from the industry, from patients, and from healthcare services. In the latest European Society of Cardiology guidelines on prevention in clinical practice, eHealth was advocated as a promising option for providing CR, while it was also pointed out that further studies in the field are needed [10]. We hope to contribute to this gap in evidence with the current study.

## Trial status

The inclusion of patients started in April 2016 and was finalized in April 2018, when all 150 patients had been included.

## Abbreviations

App: Web-based application
BMI: Body mass index
CCU: Coronary care unit
CHD: Coronary heart disease
CR: Cardiac rehabilitation
MI: Myocardial infarction
SEPHIA: Secondary Prevention after Heart Intensive Care Admission
SMS: Short text message
